#### **3.1.2 Blinding**

Although it is impossible to blind the participants and exercise coaches due to this

being a non-pharmacological intervention trial. The participants' allocation result will be replaced by using alphabet 'A', 'B' or 'C' in the first blind code and the real meaning of 'A', 'B' or 'C' will be marked in the second blind code. The project manager will declare the real meaning of group 'A', 'B' or 'C' after analysis of all data is completed. (A: The Bafa Wubu Tai Chi group, B: Tradition He-styles Tai Chi group C: control group)

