## **3.8 Data management and analysis**

### **3.8.1 Data management**

The research report form is filled in by the research object and the result evaluation personnel. The research report form consists of an activity log sheet, a blood lipid measurement sheet, a body composition measurement sheet, a physical fitness measurement sheet, and an adverse event record sheet. After the completed research report sheet is reviewed by the project manager, the data entry clerk is organized to enter the data and Unified management of the original table.

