### **3.9 Quality control**

1) Quality control of the informed consent of volunteers: Before signing the informed consent form, extensive education and communication should be carried out by the volunteer participants, so that the volunteers fully understand the content of the informed consent form.

2) Volunteer recruitment quality monitoring: strictly screen, all volunteers according to the inclusion and exclusion criteria.

3) Quality monitoring of random control and blind method: The project manager randomly grouped qualified subjects according to the number of the screener according to the random grouping sequence, properly kept the blind bottom, and unbind after the data analysis is over.

4) Quality control of the intervention process: The project manager supervises the coaching and training process of the coach, and the coach should supervise and guide the training process of the volunteers of the intervention group.

5) Quality monitoring of statistical analysis: The measurement data must be clearly filled in the research report form. Those whose results are zero and those that cannot be detected in the test should be indicated by corresponding symbols and cannot be vacated in order to distinguish them from missing values. If there is a missing value, look up

the original data, and fill it in for missing; if there is no record in the original data, notify the subject to recheck immediately; if the missing value affects the resulting judgment, the case is eliminated.

6) Data management quality control: The list of documents that the project manager must keep is checked one by one. If there are any missing items, the relevant personnel shall be required to fill in them.

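### Section 3.1.2 prints the key to the A/B/C group code that it says will stay closed until the analysis is finished

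*Protocol*

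**What the plan says.** Section 3.1.2 of the protocol opens by conceding that two parties cannot be masked: "Although it is impossible to blind the participants and exercise coaches due to this" being a non-pharmacological trial. It then sets up a code with two levels. At the first level the allocation is shown only as a letter. At the second, "the real meaning of 'A', 'B' or 'C' will be marked in the second blind code". The time of opening is fixed: "The project manager will declare the real meaning of group 'A', 'B' or 'C' after analysis of all data is completed".

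The parenthesis that closes the same paragraph reads: "A: The Bafa Wubu Tai Chi group, B: Tradition He-styles Tai Chi group C: control group".

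Section 3.9, item 3, returns to the subject under quality control. The project manager is to have "properly kept the blind bottom, and unbind after the data analysis is over".

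Sections 3.7.1 and 3.7.2 describe the outcome assessors as qualified (a qualified nurse for the lipids). They do not say that the assessors are blinded. The protocol does not say who carries out the analysis.

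**The concern.** A letter code masks only while the people who see the letters do not know what they stand for. Here the protocol promises to withhold that meaning and discloses it in the same paragraph. Section 3.9 then relies on the promise as a quality-control measure.

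At stake is whether judgements made during data handling and analysis are made without knowledge of the arms. In an open-label exercise trial that is one of the few protections still available, and it is the only one this protocol sets out. If it fails, a reader of the results cannot rely on the statement that the data were analysed under code.

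**Working it through.** No arithmetic decides this point and the protocol gives no figure to reproduce. The check is to read sections 3.1.1, 3.1.2, 3.8.1, 3.8.2 and 3.9 together.

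**1. Whom can the code mask?** Participants and coaches are ruled out by section 3.1.2. The project manager generates the sequence and telephones the results to participants (section 3.1.1), so the project manager knows the arms too. No assessor blind is stated. The code opens only after analysis, so its evident purpose is to mask those who handle and analyse the data.

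**2. What does decoding need?** Two things: a record or variable that carries the letter, and the mapping from letter to arm. The analyst must have the first, because groups cannot be compared without a group variable. The mask therefore depends on withholding the second.

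**3. What does the protocol disclose?** The complete mapping, three letters to three arms. The plan is 30 participants per group, so 3 × 30 = 90 in all. The printed key decodes any of these 90 for whom the reader also has the letter. Someone with no list of letters learns nothing from the key alone. The meaning of a single letter would identify one group, 30 of the 90.

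**4. Does other text rescue the mask?** Three statements could do so: that the printed mapping is only an example, that the letters will be redrawn before use, or that the analyst and data entry staff will not see the protocol. None appears. Section 3.9, item 3, only repeats that the code will be kept safe until the analysis is over.

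**5. Which decisions are exposed?**
- *Choice of test (section 3.8.2).* The switch between parametric and rank-based methods is tied to the Shapiro-Wilk result, which leaves little latitude.
- *Elimination of cases (section 3.9, item 5).* If a missing value cannot be recovered, the case is removed when the gap is held to affect the judgement of the result. No criterion is given, so someone has to decide, and that person may know the arm. This is the main exposure.

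**6. How large could the effect be?** The protocol gives no rate of missing values, no expected number of eliminated cases and no outcome variance. No bias can be calculated or bounded from it.

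**The case against.** The strongest reply is that the contradiction is on paper only. The analyst may never read section 3.1.2, and the primary outcomes (body composition and blood lipids) are read from instruments. The normality rule largely fixes the choice of test. Most of this stands. It limits the likely consequence and is why the point does not rank higher. It does not remove the fault, because the protocol nowhere keeps its text from the analyst, and instrument readings give no protection when cases are dropped after measurement.

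A reader might also infer more than the document supports:

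- *That blinding does not exist at all.* The code is compromised as written. Whether masking fails in practice depends on whether those who see the letters have also read the key, and the document does not say.
- *That blinded outcome assessment is broken*, with most effect on the balance tests, wall squat and six-minute walk. The protocol promises no assessor blind, so none is shown to be breached. It also does not say that the outcome sheets carry the letter. The tests named are all secondary outcomes.
- *That the forms reveal the controls.* Section 3.8.1 says that "The research report form consists of an activity log sheet, a blood lipid measurement sheet", among other sheets. It does not say that the activity log records training attendance, who fills in which sheet, or that assessors see the log.
- *That one letter gives away all 90 participants.* It does not, as step 3 of the check shows.

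**Conclusion.** The point holds for the group code. Section 3.1.2 states a masking property and defeats it in its own text, and section 3.9, item 3, repeats a commitment that cannot be relied on while the key is printed. The only masking the protocol describes is therefore compromised at the data-handling and analysis stage.

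This rests on two assumptions: that the analyst works with the group variable coded by these letters, and that the analyst may have read the protocol. The first follows from the design. The second is likely but not stated.

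The effect on the results cannot be sized. It would act mainly through discretionary elimination of cases. Severity: should fix.

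**What to change.** - Delete the parenthetical key from section 3.1.2.
- Because the present mapping has been disclosed, deletion alone is not enough. Have the code holder reassign the letters to arms at random before any coded data reach the analyst.
- State that the code holder does not carry out the analysis.
- Keep the new key outside the protocol, and away from the analyst and data entry staff, until the analysis is complete.
- Say in section 3.1.2 who is masked and until when, and make section 3.9, item 3, agree.

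The cost is one deletion, one random reassignment of three letters and a sentence or two of text. If the project manager, who now holds the code, was also going to analyse the data, one of the two tasks must pass to someone else. Sample size, visits and measurements are unaffected. The change has to come before the analysis, because masking cannot be restored afterwards.

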### **3.2 Participants**

Research subjects will be recruited from three universities, Jiaozuo Teachers College, Jiaozuo University and Henan University of Technology, Jiaozuo City, Henan Province, China. These research subjects will be male college students, selected according to China's overweight standard BMI. All participants are interested in Tai Chi activities.

#### **3.2.1 Inclusion criteria**

- 1) Age 18-23 years old
- 2) Male college students in the first or second year of university
- 3) Informed consent, voluntary participation
- 4)  $24 \leq \text{BMI} < 27.9$  (Chinese overweight standard)

Those who meet the above criteria can be included in the study.

#### **3.2.2 Exclusion criteria**

- 1) Regular long-term Tai Chi athletes
- 2) Have any sports association members
- 3) Severe cardiovascular disease or musculoskeletal system disease
- 4)  $\text{BMI} < 24$  or  $\text{BMI} \geq 28$  (Chinese overweight standard)

Those who meet any of the above criteria will not be included in the study.

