#### **3.1.1 Randomization and allocation concealment**

The eligible participants will be randomly allocated in a 1:1:1 ratio to either the Bafa Wubu Tai Chi group, tradition He-styles Tai Chi group and control group. The random allocation sequence will be generated using web programming at <http://www.randomizer.org> by the project manager. The eligible participants will be informed of their allocation result by the project manager via telephone after their baseline information has been assessed.

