#### **3.2.3 Exit criteria**

- 1) Those who can't insist on training;
- 2) Those who do not practice according to the training requirements;
- 3) Sudden illness or injury occurred during the test and cannot continue to participate in the training;

- 4) Those who voluntarily propose to quit the researcher;
- 5) The control group members practice Tai Chi during the experiment;
- 6) Those who have adverse events and are not suitable to continue practicing.

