### 3.4.3 Control group

Because the control group does not do any exercise intervention, during the 12-week experiment, all participants will be asked to keep normal diet and daily routine.

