### **3.5 Intervention time**

The Bafa Wubu Tai Chi group and the traditional He-style Tai Chi group will receive Tai Chi training 12 weeks, 3 times a week, each course is 60 minutes, including 30 minutes of Tai Chi exercises and 15 minutes of warm-up and cold down. The control group will have 1 health lecture every month, 3 times in total 12 weeks. During the 12-week experiment, all participants will be asked to keep normal diet and daily routine.

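### The entry rule tolerates casual Tai Chi practice but the exit rule for controls tolerates none, so a trait knowable at screening can become a one-arm exit after randomisation

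*Protocol*

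**What the plan says.** Five places in the protocol bear on this.

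- **Section 3.2 (Participants)** describes the recruitment pool: "All participants are interested in Tai Chi activities".
- **Section 3.2.2 (Exclusion criteria)**, item 1, excludes "Regular long-term Tai Chi athletes". Neither the regularity nor the duration has a threshold. Item 2, "Have any sports association members", would also catch a man who belongs to a Tai Chi club. No other inclusion or exclusion criterion concerns previous Tai Chi.
- **Section 3.4.3 (Control group)** says of the 12 weeks that "all participants will be asked to keep normal diet and daily routine". Section 3.5 repeats the request for all arms.
- **Section 3.2.3 (Exit criteria)**, item 5, makes it a ground for exit if "The control group members practice Tai Chi during the experiment". No minimum amount is given.
- For the Tai Chi arms, the nearest item in section 3.2.3 is item 2: "Those who do not practice according to the training requirements". It says nothing about practice before the trial or outside class.

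Participants are "randomly allocated in a 1:1:1 ratio" (section 3.1.1) and learn their allocation after the baseline assessment. The Visit 1 content listed in section 3.6 is gender, age, height, weight and BMI. Tai Chi history is not on that list.

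**The concern.** The two rules use different thresholds for the same behaviour. At entry, only regular long-term athletes and association members are turned away. After randomisation, any practice at all is a ground for exit, but only in the control arm.

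Consider a first-year student who does Tai Chi once a week with friends or takes a current course. He can be enrolled. In either Tai Chi arm, his previous practice is not a ground for exit. In the control arm, following the instruction to keep his routine brings him within exit criterion 5.

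Whether he practises could have been asked before randomisation. Left unasked, it can produce a loss that depends on the arm. If exited controls drop out of the comparison, the control arm no longer has the same mix of men as the Tai Chi arms, and randomisation no longer protects the contrast. If their data are kept, the control arm includes men exposed to Tai Chi during the trial, which tends to blur the contrast. Section 3.8.2 names unadjusted tests for the group comparisons, and section 3.6 lists no record of Tai Chi history, so affected men might be hard to identify afterwards.

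**Working it through.** **Step 1. Follow one man through the text.** He practises informally, is not a long-term athlete and belongs to no association.

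| Stage | Allocated to control | Allocated to a Tai Chi arm |
|---|---|---|
| Entry (3.2.1, 3.2.2) | eligible | eligible |
| Instruction (3.4.3, 3.5) | keep the daily routine, which includes Tai Chi | keep the daily routine, plus classes |
| Exit (3.2.3) | meets item 5 | no item applies if he follows the training |

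The asymmetry comes from the wording alone and rests on no figure.

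**Step 2. Size of a composition shift.** The protocol gives neither input, so both are assumptions: p, the share of enrolled men who practise casually, 10% to 30%; and d, their difference from the other men on an outcome, 0.3 to 0.5 SD.

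With no treatment effect, let non-practisers have mean m. A complete arm has mean (1 − p)m + p(m + d) = m + pd. A control arm without its practisers has mean m. The Tai Chi arms stay complete, so the artificial difference is p × d.

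- Low end: 0.10 × 0.3 = 0.03 SD
- High end: 0.30 × 0.5 = 0.15 SD
- If exited men are measured and analysed in the arm to which they were randomised, no one is removed and the shift is 0.

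The sign follows the sign of d, which is unknown.

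**Step 3. Put this against the planned effect.** The sample size in section 3.3 reproduces. With f = 0.40 and N = 66, λ = 66 × 0.40² = 10.56, the critical F on 2 and 63 degrees of freedom is 3.1428, and power is 0.818, as stated. If both Tai Chi arms share one mean and control differs by D, then f = D√2/3, so D = 0.40 × 3/√2 = 0.85 SD. A shift of 0.03 to 0.15 SD is then 0.03/0.85 = 4% to 0.15/0.85 = 18% of the planned effect.

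**Step 4. Check whether sample size is threatened.** Same pattern of means, power by the noncentral F:

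| Per arm (Tai Chi, Tai Chi, control) | Power |
|---|---|
| 30 / 30 / 30 (planned) | 0.926 |
| 30 / 30 / 27 (10% of controls removed) | 0.907 |
| 30 / 30 / 21 (30% of controls removed) | 0.845 |
| 24 / 24 / 21.6 (10% of controls removed, then 20% dropout in all arms) | 0.825 |
| 24 / 24 / 16.8 (30% of controls removed, then 20% dropout in all arms) | 0.747 |

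Only the last row falls below the 0.80 target. It needs the highest assumed share and a 20% dropout that counts none of these exits.

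**The case against.** **The data may not be lost.** Section 3.2.3 lists grounds for exit. It does not say that an exited man's outcomes are discarded. Section 3.6 has all participants attend Visit 3, and section 3.9 eliminates a case only where a missing value affects the judgment of the result. Analysis sets are commonly left to the analysis plan, which is not at hand. This stands: a reader might infer that the control arm will be stripped of practitioners, and the documents do not establish that. It does not remove the point, because keeping the data exchanges loss for contamination, and an analysis plan cannot change who was enrolled.

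**The routine request is general.** It can be read as asking people not to change their lifestyle, with exit criterion 5 as the specific rule for controls. That is a fair reading for most men. The conflict remains for a man whose routine already includes Tai Chi, and nothing in the eligibility criteria keeps him out.

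**Interest is not practice.** No passage shows that current practitioners will be enrolled, and the association exclusion removes some of them. This also stands. It limits the likely size without closing the gap for informal or course-based practice.

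**Sample size.** A reader might infer a shortfall, because a control arm of 30 × 0.9 × 0.8 = 21.6 is below the 22 per group in section 3.3. The documents do not support this. The 20% allowance is not limited to other causes of dropout, and even 24/24/21.6 gives power of 0.825 against the stated 0.818.

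**Dilution.** A reader might also argue that earlier practitioners have less to gain from training and so weaken the estimated effect. Randomisation spreads them over all arms, so enrolling them is an eligibility choice and not an error of validity. The documents give nothing from which to size it.

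**Conclusion.** The point holds as a mismatch between entry and exit rules. Section 3.2.2 leaves informal and course-based practitioners eligible. Section 3.2.3 item 5, read with the routine instruction in sections 3.4.3 and 3.5, makes them liable to exit in the control arm only. The result is an avoidable one-arm loss after randomisation, or contamination of the control arm if their data are kept.

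The size and direction are unknown. The range of 0.03 to 0.15 SD rests entirely on the assumed shares and differences, and applies only if exited men's data are dropped. The composition shift is zero if they are measured and analysed as randomised. The reason to act is that the problem can be prevented cheaply at screening, not that a large bias has been shown.

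**What to change.** Reconcile section 3.2.2 with section 3.2.3 item 5. Change exclusion criterion 1 so that it covers any current or recent Tai Chi practice, including a university course, over a look-back period that the sponsor fixes. Ask about it at Visit 1, before randomisation, and apply it to every candidate whatever his later allocation. Record the answer on the Visit 1 form.

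No separate criterion on accepting any of the three allocations is needed, since section 3.2.1 already requires informed consent and voluntary participation.

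The cost is one screening question and a small amendment. The downside is a slightly smaller pool among students interested in Tai Chi.

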#### **3.2.3 Exit criteria**

- 1) Those who can't insist on training;
- 2) Those who do not practice according to the training requirements;
- 3) Sudden illness or injury occurred during the test and cannot continue to participate in the training;

- 4) Those who voluntarily propose to quit the researcher;
- 5) The control group members practice Tai Chi during the experiment;
- 6) Those who have adverse events and are not suitable to continue practicing.

### 3.3 Sample size

The purpose of this study is to evaluate the effect of the newly compiled Bafa Wubu simplification Tai Chi and traditional He-style Tai Chi on the blood lipids and physical fitness of overweight college students. Therefore, using a randomized controlled trial study design (RCT). Since blood lipids are the main outcome variable of the study, however, the previous research literature did not have 3 groups of test subjects similar to this research, similar exercise intensity and similar parameters. Therefore, G Power 3.1.9.4 is used to estimate the sample size. Since the experiment is designed into three groups, select "ANOVA: Fixed effects, omnibus, one-way" in F tests, select "A priori: Compute required sample size" in Analysis, and set the effect size conventions to the maximum value  $f=0.40$ ,  $\alpha$  err prob is set to 0.05, power ( $1-\beta$  err prob) value is set to 0.80, Number of groups is set to 3. The calculation steps are as follows:

The screenshot shows the G\*Power 3.1.9.4 software window. The 'F tests' tab is selected, and the 'ANOVA: Fixed effects, omnibus, one-way' test is chosen. The 'Analysis' section is set to 'A priori: Compute required sample size'. The 'Input' parameters are: Effect size  $f = 0.40$ ,  $\alpha$  err prob = 0.05, Power ( $1-\beta$  err prob) = 0.80, and Number of groups = 3. The 'Output' parameters are: Noncentrality parameter  $\lambda = 10.5600000$ , Critical F = 3.1428085, Numerator df = 2, Denominator df = 63, Total sample size = 66, and Actual power = 0.8180744. The 'Test family' is 'F tests' and the 'Type of power analysis' is 'A priori: Compute required sample size - given  $\alpha$ , power, and effect size'. The 'Input Parameters' section shows 'Determine =>' with 'Effect size f' set to 0.40, ' $\alpha$  err prob' set to 0.05, 'Power ( $1-\beta$  err prob)' set to 0.80, and 'Number of groups' set to 3. The 'Output Parameters' section shows 'Noncentrality parameter  $\lambda$ ' set to 10.5600000, 'Critical F' set to 3.1428085, 'Numerator df' set to 2, 'Denominator df' set to 63, 'Total sample size' set to 66, and 'Actual power' set to 0.8180744. A 'Calculate' button is visible at the bottom right.

